## 4. INVESTIGATIONAL PRODUCT

### 4.1 Name and description of investigational product(s)

*Visiopharm metastasis detection app (IVDR approved)*

### 4.2 Summary of findings from non-clinical studies

Although the algorithm for detection of breast cancer metastases is IVDR approved, no clinical studies have been published so far. However, Visiopharm does provide a table on their website on a study including for 296 breast cancer cases from three clinical sites, reporting a sensitivity of 99.3% and a specificity of 100% for pathologists who are assisted by their AI-algorithm.

[https://visiopharm.com/app-center/app/metastasis-detection-ai/?gclid=EAlaIQobChMlorPrmOCi9QIVBp53Ch2nGAKLEAAYASAAEgIXLPD\\_BwE](https://visiopharm.com/app-center/app/metastasis-detection-ai/?gclid=EAlaIQobChMlorPrmOCi9QIVBp53Ch2nGAKLEAAYASAAEgIXLPD_BwE)

### 4.3 Summary of findings from clinical studies

No clinical studies have been performed so far, as only retrospective studies have been reported.

### 4.4 Summary of known and potential risks and benefits

Potential risks (zero); patients are at no risk to receive an inferior diagnosis, as the pathologists will always be the one making a definitive diagnosis. In case of doubt, IHC will always be performed.

Potential benefits: reduction of means (IHC), thereby reducing costs. Moreover, we envision improved time management, and an improved work flow for pathologists.

## **5. METHODS**

### **5.1 Study parameters/endpoints**

#### **5.1.1 Main study parameter/endpoint**

Relative risk of IHC-use per detected case of SN-metastases.

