#### 3.4 Sample size calculation

All SN-specimens assessed within the UMC Utrecht for three consecutive months (August 1st – November 1st 2021) were analyzed. In total, 83 SN-specimens were assessed, for which in 68 cases (81.9%) IHC was performed.

In 24/83 SN-specimens metastases were detected (8 macro-metastases, 8 micro-metastases, and 8 x isolated tumor cells).

- o All 8 macro-metastases were detected without IHC
- o 2/8 micro-metastases were detected without IHC
- o None of the 8 cases with isolated tumor cells were detected without IHC

We presume that the AI-algorithm will detect all metastases for which currently IHC is used. This means that for 14 metastases (6 micro-metastases + 8 ITC) no IHC will be used in the intervention group, whereas in the control group, IHC would be used. This leads to the following proportions per arm:

- $P1 = 68/83 = 0.819$
- $P2 = (68-14)/83 = 0.651$

A one-sided test was used, as we are only interested in a one-sided outcome, i.e. less IHC being performed in the AI-assisted arm. In addition, it is not likely that more IHC will be performed in the AI-assisted arm, as in both arms pathologists make the call whether to perform IHC. So even if the AI-algorithm would not recognize any metastases, the

pathologist would still look at the HE-slide and check whether there are no metastases (morphologically), which is exactly what the pathologists in the other arm are doing.

Calculations were performed in R by using the `power.prop.test` command (see below).

```
> power.prop.test(n=NULL, p1=0.819277108, p2=0.650602409, sig.level=0.05, power=0.8, alternative = "one.sided")

Two-sample comparison of proportions power calculation

      n = 83.61041
     p1 = 0.8192771
     p2 = 0.6506024
sig.level = 0.05
  power = 0.8
alternative = one.sided

NOTE: n is number in "each" group
```

We decided to be conservative and include 90 SN-specimens (i.e. from 90 patients) per arm. This will take approximately 7 to 8 months.

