### 6.1 Primary study parameter(s)

As the primary outcome measure is dichotomous, a simple Chi-squared test will be used to test for differences in the proportion of IHC-use in both arms. Furthermore, relative risks (of IHC-use) will be calculated.

For baseline comparisons between both arms, we will use the appropriate measures (parametric or non-parametric) for categorical (Chi-squared test/Fisher's exact) and continuous parameters (T-test, Mann-Whitney U test).

Although we do not expect differences in patient- and tumor characteristics between both groups, we will adjust for them if they are observed. We do not plan to perform the often used logistic regression model, but we will explore alternative models like Poisson regression with robust standard errors or log-binomial regression, as these will provide adjusted relative risks instead of odds ratio's provided by logistic regression.

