### Primary endpoint analysis

For the analysis of the primary endpoint, the proportions of IHC-use in all cases of detected SN-metastases were compared, and adjusted risks were calculated using a log-binomial regression model (1-6), with starting values provided by the simple approach suggested by Schwendinger *et al* (7, 8) and 95% confidence intervals (CI) calculated by bootstrapping (n=1,000) (1).

Potential confounders were identified a-priori during discussions with all participating pathologists. Two factors may play a role here. First how diligently a pathologist looks at the HE-section could potentially be influenced by tumor characteristics on biopsy. However, all participating pathologists stated that they virtually always look at an SN without prior looking at any of the tumor characteristics on biopsy. In this light, it is also important to mention that the SN-specimen is always assessed a day before the resection specimen of the tumor itself. Hence, many (if not all) tumor characteristics (either derived from the biopsy or the resection specimen) are unknown to the pathologist who assesses the SN-specimen. Second, some tumor characteristics may influence the visibility of metastasized cells. Two of these potential confounding factors were identified. First, the size of metastases (i.e. macro-metastases ( $\geq 2\text{mm}$ ), micro-metastases ( $< 2\text{mm}$ ) or ITC) influences their visibility to a pathologist (either with or without AI-assistance), and consequently influences the use of IHC. The same holds true for histologic subtype, as for example lobular cancer cells are known to be more difficult to identify on the HE-section.

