### Sample size calculations

Sample size calculations were based on a retrospective analysis of 83 consecutive SN-specimens from a period of three months in the UMC Utrecht. We assumed that the AI-assisted pathologist would detect all metastases without IHC for which currently IHC is needed, which are mainly micro-metastases and ITC (~15%). Of the 83 cases, IHC was used in a total of 68 cases (0.819), mainly consisting of negative cases and 14 cases of ITC and micro-metastases. We assumed that these 14 cases would be detected by the algorithm, without the need for IHC. This resulted in a presumed proportion of IHC-use in the intervention arm of 0.650 (54/83). This sample size calculation is thus built on two assumptions, being a presumed similar overall distribution of negative cases and cases of ITC, micro- and macro metastases during the trial, and a presumed proportion of IHC-use in the intervention arm based on assumptions of the accuracy of the algorithm. Therefore, the sample size calculation is in theory indirect. However, it was deemed the best way calculate clinically applicable sample sizes for this trial.

We used a one-sided significance level of 5%, as it was deemed impossible to use more IHC

after AI-assistance, and a power of 80%, resulting in a sample size of 166 SNs (83 per arm). As there are uncertainties on the assumption of the amount of metastases that the AI-assisted pathologist would detect without IHC, we decided to include 180 SNs (90 per arm) to be on the safe side.

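### The sample size and its 80% power are calculated for IHC-use among all SN-specimens, but the declared primary endpoint is IHC-use among specimens with detected metastases

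*Combined protocol and SAP*

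**What the plan says.** Two parts of the plan restrict the primary endpoint to positive specimens. Protocol 5.1.1 defines it as "Relative risk of IHC-use per detected case of SN-metastases". The SAP, under Primary endpoint analysis, states that "the proportions of IHC-use in all cases of detected SN-metastases were compared".

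The sample size uses a different base. Protocol 3.4 starts from the pilot: "In total, 83 SN-specimens were assessed, for which in 68 cases (81.9%) IHC was performed". It then assumes that "for 14 metastases (6 micro-metastases + 8 ITC) no IHC will be used in the intervention group", which gives "P2 = (68-14)/83 = 0.651". The SAP repeats the 68/83 against 54/83 comparison. Both are set at one-sided 5% and 80% power, and both round up to 90 specimens per arm.

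Protocol 6.1 says that "a simple Chi-squared test will be used to test for differences in the proportion of IHC-use in both arms". It does not say which specimens form the proportion.

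The SAP concedes that its calculation is indirect. It gives two reasons, the assumed case mix and the assumed accuracy of the algorithm. It does not mention that the denominator differs from that of the endpoint. Neither document gives an expected number of positive specimens per arm, or a power for the endpoint in 5.1.1.

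**The concern.** A power statement belongs to one comparison: one numerator, one denominator and one number of analysed units. Here the calculation counts all specimens, most of them negative, while the endpoint drops the negatives. In the pilot 83 − 24 = 59 of the 83 specimens had no metastasis.

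Two things are at stake. First, a reader who relies on the 80% is relying on a figure for another endpoint, with another effect size and more than three times as many units per arm. Second, because 6.1 leaves its denominator open, a reader cannot tell from that section which proportion the confirmatory chi-squared test uses. If the two candidates differ much in effect size and power, the choice can decide the conclusion.

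**Working it through.** **Inputs (protocol 3.4).** 83 specimens, IHC in 68; "In 24/83 SN-specimens metastases were detected"; 14 of those 24 needed IHC (6 micro-metastases and 8 isolated tumor cells); one-sided 5%; 90 per arm. A metastasis is called rescued below if it would have needed IHC but is found on H&E with AI assistance. The plan assumes 14 of 14 rescued.

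**Formula (as in `power.prop.test`, no continuity correction).** With p̄ = (p1 + p2)/2:

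n = [z(α)·√(2p̄(1−p̄)) + z(β)·√(p1(1−p1) + p2(1−p2))]² / (p1−p2)²

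power = Φ{[√n·|p1−p2| − z(α)·√(2p̄(1−p̄))] / √(p1(1−p1) + p2(1−p2))}

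**Step 1: the plan's figure.** p1 = 68/83 = 0.8193 and p2 = 54/83 = 0.6506, so n = (1.0267 + 0.5156)² / 0.1687² = 83.61. This reproduces the stated value with all specimens as denominator. Power at 90 per arm is 82.5% one-sided.

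**Step 2: the declared endpoint on the same assumptions.**
- Control 14/24 = 0.583, intervention 0/24 = 0.
- n = (1.0573 + 0.4149)² / 0.5833² = 6.4, so about 7 positives per arm.
- Expected positives per arm: 90 × 24/83 = 26.0. The binomial 95% range is 18 to 35, assuming the pilot prevalence of 28.9%.
- The assumed relative risk is 0/0.583 = 0 among positives, against 0.651/0.819 = 0.79 among all specimens.

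**Step 3: power when fewer than 14 are rescued.** The documents give no range, so the rates below 14 of 14 are assumptions. With k rescued, the intervention proportion is (14−k)/24 among positives and (68−k)/83 among all specimens.

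| Rescued | Positives: p2 (RR) | Power, 26/arm, one-sided | two-sided | All: p2 (RR) | Power, 90/arm, one-sided | two-sided |
|---|---|---|---|---|---|---|
| 14/14 | 0 (0) | >99.9% | >99.9% | 0.651 (0.79) | 82.5% | 73.1% |
| 10/14 | 0.167 (0.29) | 94.7% | 89.7% | 0.699 (0.85) | 59.8% | 47.2% |
| 8/14 | 0.250 (0.43) | 80.0% | 69.4% | 0.723 (0.88) | 45.8% | 33.6% |
| 7/14 | 0.292 (0.50) | 69.0% | 56.6% | 0.735 (0.90) | 38.7% | 27.3% |

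**Step 4: sensitivity.** With 18 positives per arm, the one-sided power in the four rows is 99.8%, 85.0%, 65.8% and 55.0%. With 35 it is >99.9%, 98.5%, 89.6% and 80.3%. The normal approximation is rough at 26 per arm. By exact enumeration at 8 of 14, one-sided power is 82.9% for the uncorrected chi-squared test and 74.5% for Fisher's test.

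**The case against.** The strongest defence is that the mismatch is harmless. On the plan's own assumption the declared endpoint needs about 7 positives per arm and should have about 26. One-sided power stays near 80% even if only 8 of 14 are rescued. Sizing on all specimens was therefore the more demanding choice, and the SAP adds specimens because it is unsure how many metastases the AI-assisted pathologist will find.

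The defence also holds that positives-only is the sensible primary. Section 2 says the only direct benefit of the algorithm is to confirm metastases that would otherwise need IHC. Specimens negative on H&E get IHC in both arms by design, so including them dilutes the contrast.

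Most of this stands. It means that 90 per arm is not shown to be inadequate, and it supports keeping the endpoint in 5.1.1. It does not make the power statement correct. The SAP's caveat about an indirect calculation names case mix and accuracy but not the denominator, and the expected number of positives, on which the real power depends, is given nowhere.

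**Conclusion.** Wrong as written. The stated 80% power and its 0.819 against 0.651 justification belong to IHC-use among all specimens, not to the endpoint declared in 5.1.1 and analysed in the SAP. The declared endpoint rests on about 26 units per arm rather than 90. Its one-sided power runs from above 99.9% down to 69% as the rescue rate falls from 14 to 7 of 14, against 82.5% down to 39% for all specimens. At 10 of 14, one comparison would probably succeed (about 95%) and the other is much less certain (60%).

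These figures assume the pilot prevalence, the pilot control rate of 14/24, equal arms and independent specimens. The rescue rates below 14 of 14 are illustrative.

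A reader might infer more than the documents support:
- **That the trial is underpowered.** On the plan's own assumptions the declared endpoint has far more than 80% power.
- **That the all-specimen design misses its own 80%.** It does so only two-sided (73.1%). At the planned one-sided 5% it has 82.5%. Sidedness is a separate gap: neither 6.1 nor the SAP's software section names a side.
- **That the test in 6.1 uses all specimens.** The section names no denominator, and it refers to the primary outcome measure, which 5.1.1 defines among positives.
- **That the narrower denominator was introduced afterwards.** The SAP is in the past tense and cites a page accessed in May 2023, but the prospectively written protocol already has this denominator in 5.1.1.
- **That the primary should become all-specimen IHC-use.** That would lose power at every rescue rate above. It would not remove the effect of a false-positive H&E call, which lowers IHC-use under either denominator. It would also follow results that the SPIRIT-AI checklist says were presented in 2023.

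**What to change.** 1. Keep the endpoint in 5.1.1 as primary. In 6.1, state that the chi-squared test and the relative risk are calculated among specimens with detected SN-metastases.
2. In 3.4 and the SAP, relabel the 0.819 against 0.651 calculation as applying to all-specimen IHC-use, or replace it. For the declared endpoint, give the expected positives per arm (about 26, range 18 to 35) and the power over a range of rescue rates. State whether the test is one- or two-sided and use that side throughout.
3. Report all-specimen IHC-use by arm, with its relative risk (0.79 on the plan's assumptions), alongside the primary result and labelled as secondary. It sits naturally beside the stain count and cost already listed in 5.1.2.

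The cost is a few sentences, one short table and one extra reported proportion. No new specimens or data are needed. Because results have already been presented, the restated power should be marked as a later clarification and not as a prospective calculation.

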#### **5.1.2 Secondary study parameters/endpoints (if applicable)**

##### 1. Workflow improvements:

- Difference in spent time per SN-specimen between both arms.
- Difference in absolute number of IHC-stains and subsequent costs between both study arms.

##### 2. Pathologist performance

- Sensitivity and negative predictive value of the pathologists on the HE-slides, stratified for type of metastases (isolated tumor cells, micro metastases, macro metastases).
- AI-user experience (questionnaire).

##### 3. AI-performance

- standalone AI-performance in the intervention arm
- retrospective standalone AI-performance in the control arm
- combined overall standalone AI-performance.

### **5.2 Study procedures**

Main endpoint: See figure 1.

Secondary endpoint 1: Time is measured by stopwatch (researcher sitting next to pathologist), absolute number of stains is recorded and costs are calculated with a price of €25 per stain.

Secondary endpoint 2: Sensitivity and negative predictive value are calculated per type of metastases, AI user experience is determined by an online questionnaire.

Secondary endpoint 3: AI-performance is determined by the researcher in consultation with a pathologist in case of doubt.

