### **Proposed clinical workflow (see figure below)**

Pathologists in the control arm will perform assessment according to the current clinical workflow. Pathologists in the AI-intervention arm will assess the HE-specimens digitally after the algorithm has assessed these. The output of the algorithm will be available to the pathologist when they assess the H&E specimen. Like in the control arm, if no metastases or tumors are detected on the H&E slide with AI assistance, additional IHC stainings are being performed in all cases, to ensure no metastases or tumors are being missed.

Therefore, the only direct benefit from the algorithm, in this first clinical introduction of AI tumor detection, will be the confirmation of metastases or tumor by the AI-assisted pathologist, in cases for which the non-AI-assisted pathologist would need IHC.

In a second phase, as the reference standard (IHC) will have been determined in all cases for which the AI-assisted pathologist concluded that no tumor or metastases were morphologically visible, we will be analyzing the safety of omitting IHC in these cases.

[figure not shown]

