### Secondary endpoint analysis

For the secondary endpoint measurements of pathologist and AI-performance, sensitivity and negative predictive values (NPV) are presented as point estimates. Results of the questionnaire on the SN-workflow of Dutch pathology laboratories were summarized by frequencies and percentages. Results of the questionnaire among participating pathologists were averaged and presented per question.

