| Blinding (masking)                                | 17a  | Who will be blinded after assignment to interventions (for example, trial participants, care providers, outcome assessors, data analysts), and how                                                                                                                                                                                                                                                                             |                |  | Not applicable, there was no blinding.                                                       |
|                                                   | 17b  | If blinded, circumstances under which unblinding is permissible, and procedure for revealing a participant’s allocated intervention during the trial                                                                                                                                                                                                                                                                           |                |  |                                                                                              |
| Methods: data collection, management and analysis |      |                                                                                                                                                                                                                                                                                                                                                                                                                                |                |  |                                                                                              |
| Data collection methods                           | 18a  | Plans for assessment and collection of outcome, baseline, and other trial data, including any related processes to promote data quality (for example, duplicate measurements, training of assessors) and a description of study instruments (for example, questionnaires, laboratory tests) along with their reliability and validity, if known. Reference to where data collection forms can be found, if not in the protocol |                |  | These can be found in the Study protocol, reporting summary and in our baseline Table 1.     |

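### Standalone AI performance is scored by judgement without stated masking and reported only as sensitivity and NPV point estimates, so lenient scoring and false flags would be hard to see

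*Combined protocol and SAP*

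**What the plan says.** Protocol section 5.1.2, item 3, lists three estimates: "standalone AI-performance in the intervention arm", "retrospective standalone AI-performance in the control arm" and "combined overall standalone AI-performance". Section 5.2 gives the method in one sentence: "AI-performance is determined by the researcher in consultation with a pathologist in case of doubt". The same section places a researcher at the timed reads ("Time is measured by stopwatch (researcher sitting next to pathologist"); the documents do not say whether this is the person who scores the AI. SPIRIT-AI checklist item 17a reads "Not applicable, there was no blinding".

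The protocol names no metric for the AI. The SAP, under Secondary endpoint analysis, does: the sentence begins "For the secondary endpoint measurements of pathologist and AI-performance, sensitivity and negative predictive values (NPV" and goes on to say that these are given as point estimates. Specificity, positive predictive value and confidence intervals are not mentioned. Checklist item 22, on analysing AI performance errors, is marked not applicable.

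On the reference standard, the Proposed clinical workflow in protocol section 2 says of the AI arm: "The output of the algorithm will be available to the pathologist when they assess the H&E specimen". A negative AI-assisted read is followed by IHC in every case. A positive read is not, as in the current workflow.

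**The concern.** Three features of the plan bear on how far the AI performance figures can be trusted.

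- **Scoring.** Whether the algorithm found a metastasis is left to one person's judgement, with a second opinion only when that person feels doubt. In the control arm the scoring is retrospective, so the diagnosis may already be known. Nothing in the documents keeps it from the scorer.
- **Metrics.** Sensitivity and NPV both reward an algorithm for flagging freely. A tool that raises many false alarms can score well on both, and without intervals the reader cannot see how few positives lie behind each figure.
- **Reference.** In the AI arm, a specimen called positive on H&E is labelled by a reader who saw the AI output. If that reader accepts a false flag, it is counted as a true detection by the algorithm.

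At stake is the third secondary objective: the estimate that others would use to judge the algorithm itself.

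**Working it through.** **The plan's own figure.** The documents give no precision or sample-size figure for AI performance. Their only calculation is for IHC use (protocol section 3.4), and it reproduces. With p1 = 68/83, p2 = 54/83, mean 0.7349, one-sided 5% and 80% power:

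n = [1.645·√(2·0.7349·0.2651) + 0.842·√(0.1481 + 0.2273)]² / 0.1687² = 83.61 per arm, as stated.

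**Expected counts at 90 per arm**, from the case mix in section 3.4:
- Positives: 90 × 24/83 = 26.0 per arm, 52.0 pooled.
- Negatives: 90 × 59/83 = 64.0 per arm. In the retrospective series, only 68 − 14 = 54 negatives had IHC, and 90 × 54/83 = 58.6. The expected number of IHC-verified negatives is therefore 59 to 64 per arm.

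**Effect of one lenient call.** One miss rescored as a hit adds 1/26 = 3.8 points of sensitivity in one arm and 1/52 = 1.9 points pooled.

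**What sensitivity and NPV show about false flags.** With prevalence 0.289, NPV = Sp(1 − prev) / [Sp(1 − prev) + (1 − Se)·prev]. The documents give no standalone sensitivity or specificity, so these are assumed values:

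| Se | Sp | NPV | PPV |
|---|---|---|---|
| 1.00 | 0.95 | 1.000 | 0.891 |
| 1.00 | 0.10 | 1.000 | 0.311 |
| 0.95 | 0.90 | 0.978 | 0.794 |
| 0.95 | 0.50 | 0.961 | 0.436 |
| 0.80 | 0.90 | 0.917 | 0.765 |
| 0.80 | 0.50 | 0.860 | 0.394 |

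At Se = 1 the second term of the denominator is zero, so NPV is 1 for any Sp above zero. In counts, 64 negatives give about 6 false flags at Sp = 0.90 and 32 at Sp = 0.50, and the planned report would be the same in both cases.

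**Effect of the AI-assisted reference.** Let P be the positives, N the negatives and f the share of false flags accepted as metastasis without IHC. Then:

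apparent Se = (Se·P + f·N(1 − Sp)) / (P + f·N(1 − Sp)).

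The largest case in the range Se 0.70–0.90, Sp 0.50–0.90, f 2–10% is Se = 0.70, Sp = 0.50, f = 10%. Accepted false flags are 0.10 × 64.0 × 0.50 = 3.2.
- AI arm: (18.2 + 3.2)/(26.0 + 3.2) = 0.733, a rise of 3.3 points.
- Pooled: (36.4 + 3.2)/(52.0 + 3.2) = 0.717, a rise of 1.7 points.

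The smallest rises in the range round to zero. At f = 25% the largest rises are 7.1 points (AI arm) and 4.0 points (pooled). NPV does not change by this route, because only flagged specimens are involved.

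**Precision** (exact 95% intervals for illustrative counts):
- Sensitivity 23/26 = 88.5%: 70% to 98%.
- Sensitivity 47/52 = 90.4%: 79% to 97%.
- Specificity, approximate half-width 1.96·√(Sp(1 − Sp)/n): at Sp = 0.80, 9.8 points (n = 64) to 10.2 points (n = 58.6). At Sp = 0.90 it is 7 to 8 points, and at Sp = 0.50 it is 12 to 13 points.

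**The case against.** The strongest reply is that a reader might infer more from these passages than they support.

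- *The AI arm has no reference independent of the AI.* This does not hold. It applies only to H&E-positive specimens. Every AI-assisted negative gets IHC, so metastases missed by both algorithm and pathologist remain detectable, and protocol section 4.4 adds IHC in case of doubt. Nor can one say that all 26 expected positives would lack IHC and that sensitivity is inflated. All 26 lack IHC only if every metastasis is seen on H&E, and under the plan's presumption that the algorithm detects them all, sensitivity is already 100%.
- *The scorer knew the IHC result.* The documents do not say so. The checklist entry on blinding is general, and the checklist refers the description of the AI output to a figure and a methods text that are not in these documents. What stands is that no masking or scoring rule is stated.
- *One call shifts the result by about 11 points.* That would apply to isolated tumour cells alone (about 9 per arm). Stratification by metastasis type is planned for the pathologists, not for the AI.
- *An algorithm that flags everything would look perfect.* Its NPV would be undefined, which would expose it. When sensitivity is below 1, specificity can also be back-calculated from sensitivity, NPV and prevalence. At a sensitivity of 1, which is close to what the plan presumes, it cannot.

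Two further points are fair. The arms are already reported separately, so the control-arm figure can be read alone. Sensitivity and NPV also suit the question of whether IHC could be omitted in negatives. Neither point supplies a scoring rule, masking, a measure of false alarms or an interval.

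**Conclusion.** The point holds as a weakness in how a secondary endpoint is measured and reported. It is not a demonstrated bias.

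The two firm parts are judgement-based scoring without stated masking, where one call is worth 3.8 points per arm or 1.9 pooled, and the lack of a planned specificity or interval. The AI-assisted reference is a lesser part: about 0 to 3.3 points in the AI arm and 0 to 1.7 pooled if 2 to 10% of false flags are accepted.

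The counts assume that the retrospective case mix recurs at 90 per arm. Sensitivity, specificity and the acceptance rate are assumptions, because the documents give none of them for the algorithm alone. The comparison of IHC use between arms and the sample size are not affected.

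**What to change.** Change protocol section 5.2 and the SAP's Secondary endpoint analysis as follows.

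1. **Scoring rule.** Score the locked version 2.0 output (the version named in the checklist) by a rule written in advance. In a reference-positive specimen, a flag counts as a detection only if it matches the location of the metastasis. A rule that accepts any flag would credit flags in the wrong place.
2. **Masking.** Record the flags with IHC and the final report hidden, preferably by someone who did not sit in on that read. Apply the location match afterwards.
3. **Reporting.** Give 2x2 counts by arm, with sensitivity, NPV and specificity and exact 95% intervals. The IHC already done on H&E-negative reads supplies about 59 to 64 verified negatives per arm.
4. **Lead estimate.** Name the control-arm result, whose reference is independent of the AI, as the lead, with the AI-arm and pooled results as supportive.

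The SAP is written in the past tense. If scoring is already done, the counts and intervals can still be reported, and flags can be re-recorded under masking if the output was kept.

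The cost is somewhat more scoring work and a wider interval for the lead estimate, since it rests on about 26 positives rather than 52 (in the examples above, 28 points wide instead of 18). No new specimens or stains are needed.
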